#### Secondary outcome measures

##### Cognitive measures

Cognitive functioning will be assessed using the MACFIMS battery [33] and the Multiple Sclerosis Neuropsychological Screening Questionnaire (MSNQ) [43]. The MACFIMS battery consists of the following tests: Dutch adaptation of the Controlled Oral Word Association Test (COWAT); Dutch Letter Fluency Test [44, 45], Judgement of Line Orientation (JLO) [45], Dutch version of the California Verbal Learning Test, second edition (CVLT-II) [46–48], Brief Visuospatial Memory Test-Revised (BVMT-R) [49], Paced Auditory Serial Addition Test (PASAT) [50], Symbol Digit Modalities Test (SDMT) [51], and the Sorting Test from the Delis-Kaplan Executive Function System (DKEFS) [52]. The SDMT and PASAT include the adaptations from Rao [53]. To test for performance validity, the Amsterdam Short Term Memory Test (ASTM) [54] and the Rey 15-Item Test [55] will be assessed. The Rey 15-Item Test will only be assessed if the total score on the ASTM indicates underperformance (a cut-off of ≤ 84 will be applied).

##### Work measures

Measures reflecting on work include work participation and productivity, assessed using the Work Productivity and Activity Impairment Questionnaire: General Health [56], work difficulties, using the Multiple Sclerosis Work Difficulties Questionnaire [57, 58], the capability to carry out work activities, assessed with the Capability Set for Work Questionnaire [39] which has been used in previous studies with workers with MS [38], and quality of working life, which will be assessed with the valid and reliable Quality of Working Life Questionnaire for Cancer Survivors [59] which has been used in multiple patient populations [60–62].

##### Structural and functional brain measures

The MRI scan features an expanded clinical protocol, focused on brain and lesion volumes and structural and functional connectivity. Lesion masks and volumes will automatically be detected on 3D-FLAIR [63]. Grey matter volume, white matter volume and total brain volume will be determined using FSL-SIENAX, after lesion filling [64] on the 3DT1. Volumes of the deep grey matter structures will be determined using FIRST [65], which will also be subtracted from SIENAX-derived segmentations to derive total cortical volume. Cortical thickness will be determined using Freesurfer (Charlestown, Massachusetts).

Diffusion Tensor Imaging (DTI) will be performed to investigate the microstructural integrity of the white matter [66]. Tract Based Spatial Statistics (TBSS, FSL) will be used to investigate structural integrity across the main white matter tracts in the brain [67]. Furthermore, probabilistic tractography using MRTrix will be used to visualise specific tracts in the white matter to determine structural connectivity and the volume of the specific white matter tracts of interest [68–70].

The amplitude of regional functional activation will be determined using blood-oxygen level dependent (BOLD) response during an episodic memory encoding task. The task has been specifically developed to assess memory function and robustly evokes brain activation in the hippocampus [71, 72], showing hippocampal changes in MS. It makes use of an event-related design of which only the correctly remembered items will be modelled (to ensure proper attention). The task contains different landscapes which have to be judged to be tropical landscapes or non-tropical landscapes. A retrieval task will be held after the MRI scanning has finished. FSL-FEAT will be used to analyse the BOLD responses for the correctly remembered items.

Resting-state fMRI will be used to assess functional connectivity (FC). Images will be pre-processed using FSL and corrected for motion using ICA-AROMA. FC will be calculated by correlating the averaged time series of brain regions. These regions are defined using the cortical Brainnetome atlas, and the deep grey matter atlas that is part of FIRST. Subsequently, all pair-wise connectivity scores will be corrected for the whole-brain mean, to deal with individual fingerprint effects [73]. Dynamic FC will be quantified by separating time series into sliding windows, calculating the variability over time of functional connectivity strength [74]. Static and dynamic FC patterns will be summarized across regions forming separate resting-state networks, such as the default-mode and fronto-parietal networks [75]. In addition, we will use connectivity patterns to calculate measures of static and dynamic network topology, such as global and local efficiency, using the Brain Connectivity Toolbox (BCT) in Matlab (Natick, Massachusetts: The MathWorks Inc.) [76]. Network topology will also be assessed using eigenvector centrality mapping, which determines the network importance of individual regions, which was previously validated for MS [77].

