#### Strengthening the brain

‘Strengthening the brain’ is a lifestyle intervention which combines physical exercise with cognitive training.

For the exercise component, participants receive exercise and lifestyle coaching (part in kind contribution of Personal Fitness Nederland, Fit for Life programme, www.personalfitnessnederland.nl) where one-on-one training will be provided at one of the 94 studios of Personal Fitness Nederland (PFN). Every session will exist of a combination of cardio (aerobic) and strength (anaerobic) training dependent on the goals of the participant. At the start of the programme an intake will take place, where the physical fitness of the participant will be determined, and attention will be paid to specific health issues and goals of the participant. Sessions will be made increasingly more challenging. Each session will start with weighing the participant followed by 30 min of exercise in a studio where no other people are present, guaranteeing full attention to the participant. Next to the weekly face-to-face sessions, participants are asked to perform pre-set exercises at home twice a week (20 min each) which are guided by instruction videos on an online platform. A quantitative assessment of the adherence (how many sessions attended and progress between training sessions) will be done by the lifestyle coach and participants will write down their goals concerning exercise and diet for the upcoming week in a personal log. Lifestyle coaches will also provide participants with diet schemes and mental coaching. This will also be recorded using the personal log.

For the cognitive component, participants will follow cognitive training using a Dutch home-based computerised cognitive training, BrainGymmer^©^ (https://www.Braingymmer.com), which has been used in multiple studies [34–37]. A variety of cognitive functions are trained (information processing speed, spatial memory, working memory, executive functioning) rather than one cognitive function in particular. The cognitive training will focus on the cognitive function that was most impaired on the neuropsychological assessment at baseline. The training has an adaptive mechanism, which will adjust to the participant’s performance level to make it challenging for all participants. The programme will log training time and the percentage of correctly performed games. Participants are instructed to train for 60 min per week.

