### Statistical analysis

Data will be analysed using R (R Core Team, Vienna, Austria) and Rstudio version 4.2 or higher (PBC, Boston, MA) and/or SPSS version 28 or higher (IBM, Armonk, NY). Analyses will be performed according to intention-to-treat and per-protocol. The main focus of the analyses will be on the intention-to-treat analysis, as this will reduce bias and better represents daily practice. A per-protocol analysis will be performed to evaluate the effect of the intervention on itself, supplementary to the intention-to-treat analysis. Data will be included in the per-protocol analysis if the participant completed the intervention. The alpha level will be set at a statistical threshold of α = 0.05, corrected for multiple comparisons when applicable. GAS will be used to discriminate between responders and non-responders concerning the interventions.

For the outcome cognitive functioning we will calculate a reliable change index (RCI) for each cognitive test based on the enhanced usual care group. Using the RCI scores allows us to correct for learning effects. An RCI score above + 1.64 or below -1.64 is assumed to reflect significant improvement or decline, respectively [5, 103]. The psychological and work functioning data will be obtained via questionnaires and will be analysed as continuous variables together with the physiological data. MRI images will be analysed using FSL (https://fsl.fmrib.ox.ac.uk) and Freesurfer (Charlestown, Massachusetts). Data obtained (atrophy, white matter integrity, task-specific brain activation and brain connectivity) will be exported to Rstudio after which mixed-model analyses will be performed.

Missing data will be minimised by using digital questionnaires, that prompt participants to answer each question before being allowed to proceed. For other outcome measures, multiple imputation will be used for missing baseline and follow-up data. Outliers will be identified and excluded from the main analysis.

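### Modelling only the remembered items in the memory-task fMRI makes the activation estimate depend on how many items were remembered, if forgotten items evoke a response

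*Protocol article*

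**What the plan says.** The rule is in the protocol article, *Structural and functional brain measures*. The outcome is an amplitude: "The amplitude of regional functional activation will be determined using blood-oxygen level dependent (BOLD) response during an episodic memory encoding task". Every landscape calls for a response in the scanner: "The task contains different landscapes which have to be judged to be tropical landscapes or non-tropical landscapes". Remembered and forgotten items are told apart only afterwards: "A retrieval task will be held after the MRI scanning has finished".

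On the model the article states: "It makes use of an event-related design of which only the correctly remembered items will be modelled (to ensure proper attention". It then adds: "FSL-FEAT will be used to analyse the BOLD responses for the correctly remembered items". It mentions no regressor for forgotten items, no contrast of remembered against forgotten items, and no adjustment for the number remembered.

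*Statistical analysis* takes the result forward: "Data obtained (atrophy, white matter integrity, task-specific brain activation and brain connectivity) will be exported to Rstudio after which mixed-model analyses will be performed".

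**The concern.** Restricting interest to remembered items is sound, and the stated reason (attention) is a fair one. The difficulty is doing so by leaving the other items out of the model. A general linear model does not delete unmodelled events; their response remains in the signal. Remembered and forgotten items share one sequence, so when one kind is on screen the other is not, and their regressors are negatively correlated. Omitting a regressor with a positive true effect then biases the other coefficient downward.

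The share forgotten is set by the participant's memory at that visit, which is measured after randomisation at every follow-up. The size of the bias therefore moves with memory performance. If one arm came to remember more landscapes than another, the activation measure could differ between arms although the response per remembered item had not changed. Randomisation does not protect against this.

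**Working it through.** The article gives no figure to reproduce. The check asks what the stated rule returns when the true remembered-item response is fixed.

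**Inputs from the article.** Event-related design; all landscapes judged; only remembered items modelled; FSL-FEAT used for the analysis.

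**Assumed, because the article does not give them.** 50 items of 3 s in random order, repetition time 2 s, double-gamma haemodynamic response, 100 s high-pass cosine set, no noise. Gaps between onsets, number of null trials, and the forgotten-item response *r* (as a fraction of the remembered-item response) were varied.

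**Formula.** Let x_R and x_F be the convolved regressors for remembered and forgotten items. The signal is y = 1.00·x_R + r·x_F. Fitting x_R alone (with intercept and drift terms) gives

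estimate = 1.00 + r·γ,

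where γ is the slope of x_F on x_R given the intercept and drift terms. γ is negative and moves towards zero as fewer items are forgotten.

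**Results for a rise from 70% to 80% remembered** (true value 1.00 throughout; repeat runs differ by about 0.01 to 0.02):

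| Gaps | r | Null trials | 70% | 80% | Relative change |
|---|---|---|---|---|---|
| 4-8 s | 0.8 | 0 | 0.45 | 0.53 | 0.08/0.45 = +18% |
| 4-8 s | 0.8 | 25 | 0.75 | 0.82 | 0.07/0.75 = +9% |
| 10-18 s | 0.8 | 0 | 0.80 | 0.85 | 0.05/0.80 = +6% |
| 4-8 s | 0.2 | 0 | 0.86 | 0.88 | 0.02/0.86 = +2% |
| 10-18 s | 0.2 | 0 | 0.95 | 0.96 | 0.01/0.95 = +1% |
| any | 0 | any | 1.00 | 1.00 | none |

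**Consistency check.** Row 1 implies γ = (0.45 − 1)/0.8 = −0.69 at 70% and (0.53 − 1)/0.8 = −0.59 at 80%. Using these with r = 0.2 gives 1 − 0.2 × 0.69 = 0.86 and 1 − 0.2 × 0.59 = 0.88, which is row 4.

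**Sign.** If forgotten items evoked a negative response, the direction would reverse. With r = −0.2 and gaps of 4-8 s the estimate goes from 1.14 to 1.12.

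**A second set of assumptions** (60 items, r = 1.0) gives the same direction. From 70% to 90% remembered the estimate rises from 0.23 to 0.47 with gaps of 4-6 s, from 0.67 to 0.86 when 30 null trials are added, and from 0.82 to 0.93 with gaps of 12-20 s. At 100% remembered it is 1.00 in each.

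**With x_F as a second regressor** the remembered-item estimate is 1.00 in every setting run.

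**The case against.** The best defence is that the article is condensed. It describes the task in a few sentences, and modelled may simply mean contrasted, with forgotten items carried as a nuisance regressor in the full protocol. That is possible, and if so one clarifying sentence settles the matter. But the article does not merely leave a detail out: it states that only remembered items enter the model, and nothing elsewhere in it supplies the missing regressor.

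The second defence concerns size, and it largely stands. A reader might infer from the fast-gap case that the score is about half its true value and that a ten-point memory gain raises it by 18%. That is one corner of the range: short gaps, no null trials and a strong forgotten-item response. The article supports none of these choices. Its remark about attention even suggests that some forgotten items may have been poorly attended and may respond weakly.

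The third defence concerns the arms, and it also stands. A reader might infer that 'strengthening the brain' will show a spurious activation gain because it trains memory. The article says of the training: "A variety of cognitive functions are trained (information processing speed, spatial memory, working memory, executive functioning) rather than one cognitive function in particular". Episodic memory for scenes is not listed, training focuses on each participant's most impaired function, and no figure supports a difference between arms in landscapes remembered.

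Nor does the article name task activation as a mediator or as a predictor of response. It speaks of biological mechanisms and baseline MRI parameters in general, so a distorted mediation or prediction result is a possibility, not a finding.

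**Conclusion.** The concern holds as a conditional one. Followed literally, the modelling rule yields a remembered-item estimate that is biased downward whenever forgotten items evoke a positive response, by an amount that depends on memory performance at that visit. For a rise from 70% to 80% remembered, the resulting shift is about +1% to +18% across forgotten-item responses of 20% to 80% and the timings tried, and zero if forgotten items evoke no response. These figures rest wholly on assumed task timing, null trials and response size.

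The documents do not show that the arms will differ in the share remembered, so a biased between-arm comparison is a risk and not an established result. The outcome affected is one secondary MRI measure; the primary SF-36 analysis is untouched.

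**What to change.** In *Structural and functional brain measures*, replace the statement that only correctly remembered items are modelled with one saying that all presented landscapes are modelled in FSL-FEAT, with remembered and forgotten items as separate regressors. State that the response to correctly remembered items remains the contrast of interest, which keeps the stated purpose about attention. If the full protocol already does this, correcting the sentence is enough.

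The cost is one extra regressor in each first-level model, built from item onsets and retrieval results that the planned analysis needs anyway, and slightly less precision when few items are forgotten. Where nothing is forgotten, the two models coincide. Scanning, visits and sample size do not change.

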##### Psychological measures

Fatigue will be assessed using the Checklist Individual Strength (CIS) [78], validated in Dutch PwMS [79]. Mood and anxiety will be tested using the Hospital Anxiety and Depression Scale (HADS) [80] which has been validated in PwMS [81]. Resilience will be measured using the valid and reliable Connor Davidson Resilience Scale [82]. Perceived level of stress will be assessed using the Perceived Stress Scale (PSS) [83], validated in PwMS [84]. Social mindfulness will be assessed using the paradigm by van Doesum et al. (2013) [85], the standard assessment to measure social mindfulness. Social participation will be measured using the valid and reliable PROMIS ‘Ability to Participate in Social Roles and Activities’ item bank [86].

##### Societal costs and general quality of life

Societal costs include healthcare, patient and family, and lost productivity costs and will be assessed using the iMTA Productivity Cost Questionnaire (iPCQ) [87] and iMTA Medical Cost Questionnaire (iMCQ) [88]. Additionally, the EuroQol five-level questionnaire (EQ-5D-5L) will be used to measure general quality of life. The Dutch EQ-5D-5L tariff will be used to convert EQ-5D-5L health states to utility scores to enable the calculation of quality-adjusted life-years (QALYs) [89, 90].

##### Physical functioning

In order to examine physical functioning, balance, walking speed, endurance, grip strength, and dexterity will be assessed. Balance will be assessed using the Mini-BESTest, which has been shown to be a reliable and valid balance assessment in PwMS [91, 92]. The test contains 14 items which can be categorised into anticipatory postural adjustments, reactive postural control, sensory orientation, and dynamic gait. Each item can be scored on a 3-point scale. A total score of 28 points can be achieved, where a score < 19 induces an increased risk of falling [91]. Walking speed will be measured using the Timed 25-Foot Walk (T25FW), which is a valid and reliable measure to assess ambulatory performance [93]. Participants will walk between two cones, 7.62 m apart. Participants will perform the T25FW four times, two times as fast as possible and two times on their comfortable walking speed [94]. Endurance will be measured using the Shuttle Walk Test (SWT). It is a basic test which can be conducted with few materials. The SWT has recently been validated and is proven to be a reliable outcome measure in ambulatory PwMS [95]. For this study, the protocol of Singh et al. (1992) will be used [96].

Grip strength will be assessed using a JAMAR hand-held dynamometer and will be expressed in kilograms. Participants are asked to pinch the dynamometer in a seated position with their arm held out in a 90-degree angle two times with each hand [97]. Upper limb dexterity will be measured with the combination of the 9-Hole Peg Test (9HPT) [98] and the Purdue Pegboard Test (PPT) [99]. The 9HPT is an often-used measure for dexterity in PwMS [98]. To additionally assess bimanual motor function, the PPT is included. Grip strength, 9HPT, and PPT are valid measures for upper limb assessment in PwMS [100].

##### Blood sampling

Blood will be drawn at three timepoints and will be stored in a biobank created for this study such that markers of interest can be studied retrospectively.

##### Effectiveness and adherence of treatment protocol

A quantitative assessment of the ‘strengthening the brain’ and ‘strengthening the mind’ programmes will be conducted using the Goal Attainment Scaling (GAS) [101]. Participants will formulate, together with a researcher or work coach, three to four goals following the SMART (Specific, Measurable, Attainable, Realistic, Timely) principle. For each goal, the expected or ‘level 0’ outcome will be carefully defined at baseline. Goals will be weighted for importance and difficulty. At the end of the intervention, the participant and researcher or coach will agree upon if the level of the goal was achieved (0); slightly exceeded (+ 1) or greatly exceeded (+ 2); or if it was ‘not quite achieved’ (-1) or ‘nowhere near’ (-2). The lifestyle coach in the ‘strengthening the brain’ intervention will assess how many sessions were attended and will also assess the progress between training sessions. Similarly, adherence to the cognition training within ‘strengthening the brain’ will be logged (e.g., training time and percentage of correctly performed games). In the ‘strengthening the mind’ intervention, the work coach will note the number, duration, and form of the consults (face-to-face and/or online), the number of consults the workplace representative was involved in, the role of the workplace representative, the three identified work challenges, and the proposed solutions to these work challenges. The work coach will record for each challenge the worker indicated to what extent the challenge was successfully addressed at the end of the coaching period using the Visual Analogue Scale (VAS) ranging from 0 to 100%.

### Work Package 3: Qualitative study

A selection of stakeholders involved in the project (PwMS, lifestyle- and work coaches, neurologists, neuropsychologists, occupational physicians, and occupational therapists) will be invited for the semi-structured interviews and focus groups. The interviews aim to provide insight into the experiences of stakeholders regarding the interventions and will be planned in batches to ensure an equal number of participating patients and coaches during the whole study period, preferably within a timeframe of 3 months from the last training session to avoid recall-bias. Interviews will be based on a topic list to ensure that all relevant questions will be addressed, and will continue until saturation is reached, meaning that no new themes emerge from the analysis. In case logistical improvements are brought up during the early interviews, adjustments will be made for future participants (e.g., if participants prefer to exercise in the morning rather than in the evening). Content-wise no changes will be allowed to the interventions. It is expected that 12–15 interviews with participants and 10–12 interviews with professionals from each group will be sufficient to reach saturation. Focus groups will be organised to further understand the effects of the ‘strengthening the brain’ and ‘strengthening the mind’ interventions, and to explore factors that promote or hinder the implementation of the interventions. The focus groups will consist of 8–10 participants to ensure optimal exchange of perspectives and dialogue and a script will be prepared. First, we will organize homogeneous focus groups (with participants and professionals separately); next, a heterogeneous dialogue group will be held in which participants and professionals reflect on the experiences and outcomes together. In forming focus groups, we will include diverse participants (considering sex, age, educational level). Focus groups will be organised after the individual interviews have been conducted and analysed, and short-term quantitative measures have been assessed.

As summarised in Table 1, a total of nine focus groups will be organised. For each of the two interventions, three focus groups will be organised, one with PwMS (group 1 and 2), one with coaches (group 3 and 4), and one heterogeneous group (a combination of PwMS and coaches/supervisors, group 5 and 6). One focus group will be organised for the work supervisors for the intervention ‘strengthening the mind’ (group 7). To enable implementation of the interventions in the near future, we will also organise a focus group with (referring) health care professionals (neurologists, neuropsychologists, occupational physicians/therapists; group 8), and a mixed group of PwMS and work supervisors that participated in the interventions and coaches of both interventions and healthcare professionals to discuss what is needed to introduce the interventions in practice successfully (group 9). Interviews and focus groups will be audio-recorded and transcribed to be further analysed.

**Table 1 Tab1:** Overview of focus groups

Group number	Role
1	Participants intervention ‘strengthening the brain’
2	Participants intervention ‘strengthening the mind’
3	Coaches ‘strengthening the brain’
4	Coaches ‘strengthening the mind’
5	Heterogenous group participants & coaches ‘strengthening the brain’
6	Heterogenous group participants & coaches ‘strengthening the mind’
7	Work supervisors ‘strengthening the mind’
8	Health care professionals
9	Mixed group, participants, coaches & healthcare professionals

